#### Pilocarpine study

The pharmacological study is a four-week double-blind placebo-controlled randomized trial with an eight week unblinded extension treatment period with off-label pilocarpine eye drops with 120 patients from either hospital or nursing home setting. The study intends to evaluate the effect of locally administered oral pilocarpine drops (3 × 5 mg of pilocarpine per day) in reducing complaints of dry mouth in a palliative population at the expense of limited adverse events, as compared to placebo. A double-blind placebo-controlled randomized controlled design was chosen to minimize response bias and achieve a high level of evidence.

### Study population

#### Patients with dry mouth

In both studies, patients in the palliative phase of their disease with moderate to severe dry mouth symptoms will be invited to participate in the study. Eligibility is assessed using the following inclusion criteria: dry mouth severity ≥ 5 on a scale from 0 to 10 (NRS), a life-limiting condition or frailty [24], an age of 18 years or older and possible palliative care needs as measured by the surprise question [25]. In order to fulfill the surprise question, that is “Would you be surprised if the patient died within 12 months?”, the answer must be “No”. Patients with severe cognitive decline, with previous radiotherapy to the head-neck area and/or with Sjögren’s syndrome will be excluded. Patients with a life expectancy of ≤ 4 weeks will also be excluded due to the primary endpoint being set at 4 weeks. Lastly, in the pilocarpine study patients with mobility impairments impeding correct administration of the drops will be excluded.

#### Healthcare professionals (MEP study)

A selection of healthcare professionals working at the hospitals and nursing homes within the MEP study will be asked to answer a questionnaire about current practice in dry mouth care, either before the start of the study (intervention group) or after the start of the study (control group). This group of healthcare professionals consists of nursing home doctors, nursing home nurses and nurse specialists from the hospital-based palliative care consultation teams. In addition, upon completion of the full study period the hospital-based nurse specialists and nursing home nurses leading the patient education consultations in the intervention group will be asked to participate in a questionnaire and in focus groups regarding the feasibility of the MEP. Similarly, nurses and nurse specialists from the control group will be asked to participate in a focus group to further evaluate their experiences with current care practices and guidelines.

### Intervention and control

#### MEP study

The MEP is a patient education program and has been developed by our team to increase the use of guidelines by nurses in both hospitals and nursing homes, to strengthen awareness and knowledge in both nurses and patients and to improve management of dry mouth symptoms.

The structure and methods of the MEP were built on previous experience with patient education programs [26]. The content of the patient education program is based on existing palliative care guidelines [17–19] and has been reviewed by our multidisciplinary expert group, including palliative care researchers, an elderly care physician, a radiation oncologist, palliative care nurse specialists, an oral hygienist, a dentist and a patient representative. The program has also been piloted by two independent palliative care nurse specialists to ensure practical feasibility.

Table 1 shows the components and contents of the patient education program on dry mouth. The patient education program consists of a training for participating nurses, structured consultations with patients using the MEP handbook and patient information brochures. The MEP handbook is a guidebook, containing step-by-step plans for the initial and follow-up consultations, background information on dry mouth and oral care, conversation pointers and examples of different patient scenarios. To ensure the quality and uniformity of the patient education program, all participating nurses from the nursing homes and nurse specialists from the hospital based palliative care teams will be trained before the start of the study. This training consists of information on dry mouth characteristics, causes, consequences and treatment options. They will also learn to execute a structured MEP consultation, which includes anamnesis, oral inspection, patient education and treatment advice (Fig. 2). With each participant, these trained nurses will then execute a full MEP consultation on location at the baseline visit, and will monitor the symptoms in a shorter, structured consultation telephonically (or on location) at four different time points in week 2, week 4, week 8 and week 12 (see Fig. 1a).

**Table 1 Tab1:** Components and content of the Mouth Educational Program (MEP)

Components	Content of the components
**MEP Training**	Interactive training on dry mouth and other oral symptoms, oral care, dry mouth interventions and patient education methods. For all topics involved, see components of the MEP handbook.
**MEP Handbook**	Guidebook to use during the standardized MEP consultations, including road maps, theoretical information and example scenarios
Road maps for standardized consultations	Practical step-by-step plans for both the initial and follow-up consultations, including: 1 Anamnesis 2 Oral examination 3 Patient education 4 Treatment advice 5 Reporting
Theoretical information	Evaluation of dry mouth and other (oral) symptoms • Anamnesis • Oral examination Patient education on dry mouth • Characteristics of dry mouth • Consequences for daily life • Causes of dry mouth Oral care & other interventions • Oral care for patients with varying levels of independence, functionality and frailty • Lifestyle interventions • Causal interventions • Symptom-based interventions • Referrals Monitoring & reporting
Conversation pointers & example scenarios	Practical tips for patient education and shared decision making, and example clinical scenarios with suggestions for treatment plans and patient education topics
**Patient information brochures**	Two brochures with information on oral care and dry mouth respectively

**Fig. 2 Fig2:**
[figure not shown]
Structure of the standardized MEP consultation. Using the MEP handbook, the trained MEP nurses and nurse specialists will perform a standardized consultation, including: evaluating the dry mouth complaint by anamnesis and oral examination, providing information on dry mouth care (patient education), creating a treatment plan by shared-decision making and reporting all findings and decisions in the patient’s medical records

The control condition is CAU, meaning dry mouth care as provided by the regular care team and uninfluenced by the research. No restrictions are placed on the care received and any research procedures, such as administration of questionnaires are handled by our research team.

Usual care practices, within and outside of research settings, are generally characterized by clinical heterogeneity due to differences on the individual professional level and the institutional level in awareness, knowledge, use of guidelines, training, resources, policies and so on [27, 28]. To allow for comparison between a structured form of dry mouth care (MEP) and existing practices (CAU) in two different care settings, for explanation of results, and for identification of barriers and facilitators to implementation, we have decided to collect usual care data through a self-developed questionnaire [27–30].

The institutions allocated to the control group will be offered the MEP training after they have completed the full study period (i.e. included all patients).

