**Fig. 1 Fig1:**
[figure not shown]
Study procedures for the non-pharmacological (**a**) and pharmacological study (**b**) within the Dry mOuth Project. **a** The Mouth Education Program (MEP) study is a cluster non-randomized trial with a study period of 12 weeks and five visits per patient. **b** The pilocarpine study is a double-blind placebo randomized controlled trial with an active treatment period of four weeks and an optional expanded access period of eight weeks per patient. **c** A nested qualitative sub-study will be conducted during and after both studies. Abbreviations: CAU = care as usual, MEP = Mouth Education Program, UC = usual care; HCP = health care professionals; T0-12 = patient timeline at *t* = 0, *t* = 2, *t* = 4, *t* = 8 and *t* = 12 weeks

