#### Mouth Education Program (MEP) study

The non-pharmacological study is a cluster non-randomized trial with 228 patients divided over twelve clusters (twelve organisations) in two care settings: a hospital setting with six clusters and a nursing home setting with six clusters. Within each care setting, three clusters will be allocated to the intervention arm on a first come, first serve basis (114 patients), after which three clusters will be allocated to the control arm (114 patients). The intervention, the Mouth Education Program (MEP), will be compared to the control, care as usual (CAU) over a twelve-week period. A cluster non-randomized design was chosen to reduce between-condition contamination and to improve recruitment and logistic processes [23].

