### Study procedures

Both studies in the DROP share the same study time frame (May 2023 – December 2024), time points for data collection and study instruments. Each participant is followed for a 12-week study period with 5 research visits (on *t* = 0, *t* = 2, *t* = 4, *t* = 8 and *t* = 12 weeks) at which questionnaires will be administered (see Table 2 and Fig. 1). At the end of the 12-week study period, a selection of patients will be asked to participate in semi-structured interviews to evaluate the received care. The screening and allocation procedures are different in both studies and are described separately below.

**Table 2 Tab2:** Data collection schedule and measurement instruments

Data collection	Measurement instrument	Visit 1 *Week 0*	Visit 2 *Week 2*	Visit 3 *Week 4*	Visit 4 *Week 8*	Visit 5 *Week 12*
Baseline characteristics	Questionnaire on patient characteristics	X				
Dry mouth severity	Numeric Rating Scale (NRS) (11-point; from 0 to 10) [1, 31]	X	X	X	X	X
Dry mouth impact	Summated Xerostomia Inventory, shortened Dutch version (sXI-D, adapted) [32]	X	X	X	X	X
Oral health-related quality of life	Geriatric Oral Health Assessment Index, Dutch version (GOHAI-NL) [33]	X	X	X	X	X
Health-related quality of life	EuroQol 5 Dimensions 5 Levels (EQ-5D-5L) [34]	X		X	X	X
Functional status	Patient-reported functional status (PRFS) [35]	X	X	X	X	X
Patient-perceived effect	Global Perceived Effect, 7-point scale [36, 37]		X	X	X	X
Patient-reported medical costs	The Institute for Medial Technology Assessment (iMTA) Medical Consumption questionnaire (iMCQ, adapted) [38]	X		X	X	X
Medication changes	Changes in medication since the last visit		X	X	X	X
Adherence^a^	Short questionnaire on adherence		X	X	X	X
Side-effects^a^	Short questionnaire on side-effects		X	X	X	X

^a^This data is collected in the pilocarpine study only

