#### Primary outcomes

The primary outcome is the effectiveness of the intervention in reducing dry mouth complaints in patients with a life-limiting condition or frailty. This is measured by the percentage responders at week 4, for which a clinically relevant response is defined as at least a 2-point reduction on the 11-point numeric rating scale (NRS). The NRS is a frequently used instrument in both clinical practice and research settings to score symptom severity, such as for pain, nausea and sleep [31]. The NRS for dry mouth ranges from 0 = no dry mouth symptoms to 10 = worst possible dry mouth symptoms [1, 7].

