#### Secondary outcomes

Secondary outcomes include effect durability, (mouth-related) quality of life, patient-reported functional status, global perceived effect by participants, cost-effectiveness, adherence and side-effects. The specific research instruments per outcome used are detailed in Table 2.

Effect durability is measured by the percentage responders at week 8 and 12, as well as by changes in mean NRS dry mouth scores in the intervention versus the control group at all time-points. Effectiveness as perceived by the patient is measured by a 7-point scale (the Global Perceived Effect, GPE) [37] rating how much the patients’ condition has improved or deteriorated since the start of the study in both the control and intervention group. The global perceived effect is measured using a 7-point scale, rating how much the patients’ condition has improved or deteriorated since the start of the study for both the control and intervention group.

Changes in mouth-related quality of life is examined at all time-points between groups using two different validated questionnaires: the Geriatric Oral Health Assessment Index (GOHAI-NL) [33] and the shortened Summated Xerostomia Inventory (sXI-D) [32]. The GOHAI-NL consists of 12 oral health related items and three categories: physical function, psychosocial function and pain/discomfort. The sXI-D consists of 5 items, addressing dry mouth in general and consequences of dry mouth, such as difficulty eating and swallowing. In addition, functional status and overall quality of life are measured by a validated patient-reported functional status scale (from 0 = normal with no limitations to 4 = bed ridden, rarely out of bed) [37] and the EuroQol 5 Dimensions 5 Levels (EQ-5D-5L) questionnaire [34] respectively. The latter will also be used for the cost-effectiveness analysis and assesses quality of life in five dimensions: mobility, self-care, usual activities, pain/discomfort and anxiety/depression. The EQ-5D-5L is complemented by the iMTA (Institute for Medical Technology Assessment) Medical Consumption Questionnaire (iMCQ) for the cost-effectiveness analysis [38]. The iMCQ measures medical consumption, including medical and paramedical treatments or services, in- and outpatient care and medication.

Lastly, in the pilocarpine study the adherence and side-effects from either the pilocarpine or the placebo are measured by using short-form questionnaires.

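### The rule for training MEP control sites contradicts itself: its parenthesis permits training at the last patient's inclusion, while week-4, 8 and 12 control outcomes are still pending

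*Protocol article*

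**What the plan says.** Under Intervention and control, MEP study, the institutions in the control group "will be offered the MEP training after they have completed the full study period (i.e. included all patients"). The same section defines care as usual as "dry mouth care as provided by the regular care team and uninfluenced by the research".

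The term study period is used for follow-up elsewhere. The Fig. 1 legend describes a "cluster non-randomized trial with a study period of 12 weeks and five visits per patient", and Study procedures says: "Each participant is followed for a 12-week study period with 5 research visits". The visits are at weeks 0, 2, 4, 8 and 12.

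The outcomes that follow inclusion are the primary one, of which Primary outcomes says "This is measured by the percentage responders at week 4", and durability, of which Secondary outcomes says "Effect durability is measured by the percentage responders at week 8 and 12".

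The reason given for the design, under Study design, is: "A cluster non-randomized design was chosen to reduce between-condition contamination and to improve recruitment and logistic processes".

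**The concern.** The main clause and the parenthesis set two different dates. If the study period is the 12-week follow-up, a control site completes it when its last patient reaches week 12. If it is complete once all patients are included, that date is the last patient's week 0, up to 12 weeks earlier. Nothing else in the article makes the training wait for the outcomes.

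A coordinator who follows the parenthesis would comply with the text and could still train nurses who look after control patients with assessments pending. The literal reading is also a natural one operationally. In the control arm a researcher administers the questionnaires, so inclusion is roughly where the site's own work for the study ends.

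At stake is the contrast between the arms. The MEP works through what nurses know and do, so trained staff may change the care of control patients. That would move control results toward the intervention. It would affect late enrolees only, so it would not average out. The later visits are more open to it than week 4. The control-arm focus groups on current practice could also be affected if they were held after the training; the article does not state their order.

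**Working it through.** **Plan's own figures.** Sample size, MEP study: 181 evaluable patients, 20% dropout, 12 clusters. 181 / 0.80 = 226.25, so 227, rounded up to equal clusters: 12 × 19 = 228. This agrees with the article. The control arm is 6 × 19 = 114. None of these figures depends on the timing of the training.

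**Inputs**
- Patients per site: 19 (Sample size).
- Planned difference in responders at week 4: 25 percentage points (Sample size).
- Outcome times T: 4, 8 and 12 weeks after inclusion (Study procedures, Primary and Secondary outcomes).
- Recruitment length per site, R: not stated. Assumed to be 26, 52 or 68 weeks, with even accrual.
- Delay from last inclusion to training, L: not stated. L = 0 is the earliest date that the parenthesis permits.

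**Formula.** Share of a site's patients whose visit at week T falls after the training = (T − L) / R, limited to the range 0 to 1. Number = 19 × share.

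**Result with L = 0**

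| R (weeks) | before week 4 | before week 8 | before week 12 |
|---|---|---|---|
| 26 | 4/26 = 15% (2.9 of 19) | 8/26 = 31% (5.8) | 12/26 = 46% (8.8) |
| 52 | 4/52 = 8% (1.5) | 8/52 = 15% (2.9) | 12/52 = 23% (4.4) |
| 68 | 4/68 = 6% (1.1) | 8/68 = 12% (2.2) | 12/68 = 18% (3.4) |

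Faster accrual raises the shares: at R = 13 they are 31%, 62% and 92%.

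**Result with L = 4.** No patient has a week-4 visit after the training. For week 12 the share is (12 − 4)/R: 31%, 15% and 12% for R = 26, 52 and 68.

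**Result with L = 12.** The share is zero at every visit.

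**Upper bound on dilution at week 4.** Suppose every control patient in the first column gained the full MEP effect. The difference would then be 25 × (1 − 4/R):
- R = 26: 25 × (1 − 0.154) = 21.2 points
- R = 52: 25 × (1 − 0.077) = 23.1 points
- R = 68: 25 × (1 − 0.059) = 23.5 points

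The loss is therefore at most about 1.5 to 3.8 points over this range of R. No such figure is given for week 12, because the 25 points are stated for week 4 only.

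**The case against.** The main clause, read with the article's usual meaning of study period, already protects the control arm: a site with patients at week 2 has not completed a 12-week period. The section on healthcare professionals uses the same phrase for the timing of the evaluation without the parenthesis. On this view the fault is loose wording. That is fair as to intent, but it does not remove the problem, because the parenthesis explains the phrase and the explanation points to the earlier date.

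A reader might infer that late control patients will receive the MEP. The article does not support this. The intervention is a full consultation at baseline with structured follow-up consultations, and none is planned for control participants. What remains is possible spill-over from trained nurses into usual care.

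The percentages also combine unfavourable assumptions: no delay before training, full effect in every exposed patient, and an assumed R. Under even accrual, exposed patients would on average have only half the window between training and visit, about 2 weeks for week 4 and 6 weeks for week 12. These objections stand, and they are why the week-4 figures are upper bounds.

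Finally, the article is condensed, and a full protocol may fix the timing properly. That would be reassuring, but the sentence printed here is a stated rule and not an omission.

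**Conclusion.** The point holds as an internal contradiction with a limited possible effect. The sentence gives two incompatible dates for training control sites, and the earlier one permits what the cluster design and the definition of care as usual were meant to avoid.

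For the primary outcome the effect is small at most: the 25-point difference would fall to no less than about 21-23.5 points for R between 26 and 68 weeks, and would not change at all if training came 4 or more weeks after the last inclusion. Exposure is larger at week 12, at 18-46% of control patients with immediate training. How far that would dilute the durability result cannot be put in points, since applying the week-4 difference to week 12 has no basis in the article.

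The bias would be toward no difference, so spill-over of this kind would not create a false benefit. Nor does the text show that contamination will occur; it shows only that the rule as written allows it. All shares rest on the assumed R, even accrual and the assumed training delay.

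**What to change.** In the sentence on offering the training to control institutions, replace the parenthesis with: (i.e. after the last included patient has completed or missed the week-12 assessment and the control-arm focus group has been held).

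If any control site was trained earlier, record the training date and run a sensitivity analysis that excludes control assessments made after it.

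The cost is one sentence, and control sites wait up to about 12 weeks longer for the training. The sample size stays at 228, and no visits or procedures are added. The sensitivity analysis is needed only if a site was in fact trained early.

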#### Pilocarpine study

The pilocarpine study will investigate the effect of locally administered oral pilocarpine drops (3 × 5 mg per day) compared to placebo in reducing complaints of dry mouth in patients with a life-limiting condition or frailty.

Pilocarpine activates the muscarinic receptors, stimulating saliva secretion which in turn alleviates dry mouth symptoms. Systemic pilocarpine tablets have various parasympathomimetic adverse effects such as transpiration, flushing, headaches, dizziness and more [20]. The locally administered oral pilocarpine drops created for this study, however, are topical (non-systemic) and have previously been shown to have minimal adverse effects [21]. In our pilot study an optimal dosage regime was established of 5 mg pilocarpine in drops three times per day [21]. The placebo for this trial has the same qualitative composition, except for pilocarpine HCl, and has comparable traits in terms of texture, taste and look.

For four weeks each group will be instructed to administer 6 drops 3 times a day of either pilocarpine HCL (25 mg/ml) or placebo. Drops are administered left and right outside the molars and in front of the front teeth of the lower jaw, with 2 drops at each site of application. After the blinded 4-week active study period, every participant is offered an 8-week unblinded extension treatment period with off-label pilocarpine eye drops in order to establish longer term efficacy of pilocarpine and to offer active treatment to the placebo group (see also Fig. 1b).

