#### Pilocarpine study

The pilocarpine study was submitted through the new Clinical Trials Information System (CTIS) and approved by the Medical Ethics Committee of Maastricht University Medical Center + . The risk classification analysis showed that the pilocarpine study entails moderate risk since pilocarpine is a registered drug for oral and ocular use. Case-reports and case-series indicate that topical pilocarpine administration has none or minor side effects (irritation of mouth and tongue). The burden of xerostomia on patient well-being outweighs the risk of side effects. Small studies and case reports suggest that local application has none or only minor side effects [20]. In the experimental group, benefits of participation may include relief of dry mouth symptoms and improved (oral-health-related) quality of life. Similar to the experimental group, the control group, will be offered unblinded expanded access to pilocarpine eye drops after 4 weeks and may therefore benefit from similar results.

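### Pilocarpine study: placebo control and blinding end at week 4, so week 8 and 12 results cannot show durability or longer-term efficacy against placebo

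*Protocol article*

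**What the plan says.** **Design of the extension.** Under Intervention and control (Pilocarpine study), after four blinded weeks "every participant is offered an 8-week unblinded extension treatment period", using "off-label pilocarpine eye drops in order to establish longer term efficacy of pilocarpine and to offer active treatment to the placebo group". Study design describes the same phase as "an eight week unblinded extension treatment period with off-label pilocarpine eye drops". The Fig. 1 legend shows that it is voluntary: "an active treatment period of four weeks and an optional expanded access period of eight weeks per patient". Ethical considerations adds that "the control group, will be offered unblinded expanded access to pilocarpine eye drops after 4 weeks and may therefore benefit from similar results".

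**Follow-up.** Study procedures states: "Each participant is followed for a 12-week study period with 5 research visits". The visits are at weeks 0, 2, 4, 8 and 12.

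**Outcomes and tests.** The Effect evaluation section says that outcome measures are common to the two studies, apart from adherence and side-effects. Secondary outcomes defines effect durability by two things: the percentage of responders at weeks 8 and 12, and change in mean NRS against control at every visit. Analysis of effect evaluation tests secondary outcomes between groups at weeks 4, 8 and 12 and names GOHAI-NL, PRFS and dichotomised Global Perceived Effect. Neither section treats the pilocarpine study differently after week 4.

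**The MEP study, for contrast.** Its control arm stays on usual care: "The institutions allocated to the control group will be offered the MEP training after they have completed the full study period".

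**The concern.** The durability definition suits the MEP study, where usual care continues through week 12. In the pilocarpine study three things change together at week 4: the comparator may start active drug, blinding ends, and the product switches from drops made for the study to off-label eye drops.

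Two misreadings become possible if the plan is followed as written. A between-arm difference near zero at week 8 or 12 could be taken to mean that the effect fades, when in fact the placebo arm has caught up. Alternatively, a high open-label responder percentage could be taken as established longer-term efficacy, although nothing controls for expectation, natural course or selective continuation. Durability is a named secondary outcome, the Discussion says that long-term effects are examined, and the results are meant for a national guideline.

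**Working it through.** **1. Which measurements are affected.** NRS is collected after baseline at weeks 2, 4, 8 and 12 (Table 2). Two of these four visits fall after placebo control ends, and so do both visits whose responder percentages define durability.

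**2. Reproducing the plan's figure.** Inputs are a 2-point difference against placebo (Sample size), SD 3.8 and the stated 57 per group (Sample size, Pilocarpine study). The pilocarpine paragraph gives no alpha or power. I assume two-sided 0.05 and 80%; the MEP paragraph states alpha 0.05 and power 0.8.

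n per group = 2 × (1.960 + 0.842)² × 3.8² / 2² = 56.7, rounded up to 57. This matches, so these are reasonable planning values for the illustration.

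**3. Contrast at weeks 8 and 12.** Uptake of the extension is not stated, so it is varied. All patients are analysed in their randomised arm, and the true drug effect is 2 points throughout. Let *a* and *p* be uptake in the pilocarpine and placebo arms.

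*Case A: the drug works only while it is taken.* Expected difference = 2 × (a − p).

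| a | p | Difference (points) |
|---|---|---|
| any | equal to a | 0 |
| 90% | 70% | 0.4 |
| 70% | 90% | −0.4 |
| 100% | 50% | 1.0 |
| 50% | 100% | −1.0 |

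*Case B: most favourable, the pilocarpine arm keeps its full effect.* Expected difference = 2 × (1 − p). Power is for a two-sample t-test with 57 per group, SD 3.8 and two-sided 0.05; the standard error is 3.8 × √(2/57) = 0.71.

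| p | Difference (points) | Power |
|---|---|---|
| 0% | 2.0 | 79.5% |
| 25% | 1.5 | 55.1% |
| 50% | 1.0 | 28.6% |
| 75% | 0.5 | 10.7% |
| 90% | 0.2 | 5.9% |
| 100% | 0 | 5.0% (the test's alpha) |

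With the 60 per group to be enrolled, 50% uptake still gives only about 30% power.

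**4. Reading.** In Case A the sign and size of the difference reflect who accepts the extension. In Case B they reflect how many placebo patients accept it. In neither do they measure whether a 2-point effect over placebo lasts, although by construction it does.

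**The case against.** The article discloses the extension openly in four places and calls the trial a four-week placebo-controlled study, so a careful reader need not be misled. The outcome and analysis paragraphs are condensed text serving two studies, and the full protocol or SAP may treat the extension separately. Uptake is assumed, no power is claimed for secondary outcomes, and the illustration covers mean NRS rather than responder percentage. All of this is fair and limits the weight of the point. It does not remove it, because the article states the efficacy aim, the time points and the versus-control contrast. An SAP that followed them would carry the problem forward. Nor do placebo patients who decline the extension restore a control, since they are self-selected and unblinded.

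Four stronger readings are tempting, and the text does not support them:

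- *That week 8 and 12 NRS or responder differences are to be significance-tested in this study.* The list of outcomes for the week 4, 8 and 12 tests names GOHAI-NL, PRFS and Global Perceived Effect only. The NRS comparison with control comes from the durability definition, which specifies no test.
- *That these are confirmatory tests.* The document never calls them so, and it says that interpretation will rest mainly on clinical relevance.
- *That randomisation is broken.* Every patient is followed to week 12 and an intention-to-treat analysis is planned. The comparison by randomised arm stays valid, but for a different question.
- *That durability must be dropped from the pilocarpine study.* Maintenance of response in the original pilocarpine arm is legitimate to report if it is labelled open-label.

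**Conclusion.** The point holds as a mismatch between the extension's design and the claims attached to it. After week 4 the between-arm contrast is early versus delayed start, and responder percentages within an arm are uncontrolled. Neither measures durability against placebo. If the pilocarpine arm keeps its full effect, a true 2-point benefit appears as 1.0 point at 50% placebo-arm uptake and as zero at 100%. If benefit depends on current use, it appears as zero at any equal uptake. These sizes rest on assumed uptake, a constant effect in both periods, and the assumed alpha and power. The qualitative conclusion rests only on the stated design. The week 4 primary comparison and the sample size stand, so this is a correction that should be made to a secondary outcome. It is not a threat to the trial's main result.

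**What to change.** 1. **Intervention and control, Pilocarpine study:** restate the extension's aim as describing open-label response and tolerability on pilocarpine eye drops, and offering active treatment to the placebo arm.
2. **Secondary outcomes and Analysis of effect evaluation:** restrict pilocarpine-versus-placebo comparisons to weeks 2 and 4. Keep between-group comparisons at weeks 8 and 12 as durability for the MEP study only.
3. **Pilocarpine study, weeks 8 and 12:** report descriptively by randomised arm for all patients, including maintenance of response in the original pilocarpine arm, labelled open-label. Label any between-arm comparison as early versus delayed start.
4. **Uptake:** report how many in each arm accepted the extension.

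The cost is a change of wording in three sections and one recorded item (extension accepted or declined), with no extra patients or visits. The downside is that the pilocarpine study gives up a controlled durability claim.
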